## Background

### Phenomenology and treatment

Obsessive-compulsive disorder (OCD) is a severe mental condition which is characterized by intrusive thoughts (obsessions) and repetitive behaviors (compulsions) intended to neutralize anxiety induced by these thoughts [1]. OCD has been ranked among the 10 most debilitating disorders by the World Health Organization (WHO) and tends to be chronic without adequate treatment [48]. Both studies into pharmacological treatment, primarily with selective serotonin reuptake inhibitors (SSRIs), and studies into specific forms of psychological treatment supported the effectiveness of these treatment modalities in reducing symptoms of OCD [3]. The first-choice psychological treatment for OCD is exposure and response prevention (ERP) [31, 34, 37], a specific type of cognitive behavioral therapy (CBT) based on learning theory, which suggests that classical conditioning is responsible for the development of obsessions, whereas operant conditioning processes maintain anxiety and compulsive behaviors [27]. In ERP treatment, patients are exposed to anxiety-provoking stimuli (situations, objects, thoughts) combined with the strict prevention of performing ritual behaviors [26]. Since its introduction in 1966, the prognosis for OCD improved substantially. However, OCD remains a difficult disorder to treat. Although numerous studies have found statistically significant change and large improvements in OCD symptoms after ERP, the outcomes are sub-optimal for the majority of patients. More specifically: although about 60% of treatment completers achieve recovery, only approximately 25% of patients are asymptomatic following treatment [11, 14], which means that the majority of patients treated with ERP continue to experience distressing OCD symptoms. Furthermore, the overall effectiveness of ERP for OCD is attenuated by some limitations of the approach. As approximately 30% of patients with OCD refuse ERP or drop out from treatment prematurely, it is assumed that overall recovery rates are lower [30]. Moreover, these figures suggest that ERP might be hard to tolerate and is burdensome, which is supported by the finding that an important reason for not attempting ERP are the requirements of treatment (e.g. exposure to anxiety provoking stimuli [46]). So, although it can be concluded that ERP is efficacious, there is clearly room for improvement in the psychological treatment of OCD. It is assumed that this improvement could result from a better understanding in the mechanisms involved in the maintenance of the disorder.

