## Design and methods

### Design

We will conduct a randomized controlled trial (RCT) with a pretest–post-test (primary outcome) 6-month–30-month follow-up-design. Patients will be recruited from consecutive referrals to the Anxiety Disorders department of PsyQ, an outpatient community mental health center in the Netherlands. After screening for eligibility and informed consent, we will randomize the patients into two groups: MCT and ERP. The number of excluded patients and refusers and their reasons are registered. Participating patients will be assessed by self-report measures and semi-structured clinical interviews administered by a research assistant who is blind to group allocation at entry (pre-treatment), after the last treatment session (post-treatment – primary outcome), six months (first follow-up) after treatment completion and 30 months (second follow-up) after treatment has ended. The latter assessment is included to answer a secondary research questions on the durability of both the ERP and MCT effect on the long term. Due to a lack of studies with follow-up periods of > 1 year [9, 47], the information on longer-term effects are unknown. In case of drop-out, measurements and interviews are also administered directly after treatment had ended whenever this is possible. The study has received ethical approval from the Medical Ethical Committee of the Leiden University Medical Centre (LUMC) (protocol number NL50201.058.14) and is registered in the Dutch Trial Register (protocol number NTR4855). All data will be stored anonymously; there is a data safety and monitoring board for the study. Figure 2 shows a flowchart of the study from patient enrollment up to data analysis and reporting. This study follows the “guidance of standard protocol items: recommendations of interventional study’s (SPIRIT).” The SPIRIT figure template is displayed in Fig. 3. In addition, the SPIRIT checklist can be found in Additional file 1.

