### Participant enrollment and randomization

One hundred adult patients (aged 18–65 years) with a primary diagnosis of OCD will be recruited from consecutive referrals to the Anxiety Disorders department of PsyQ, an outpatient community mental health center in the Netherlands. Diagnosis of OCD will be established using the SCID-I [10], a diagnostic interview based on the DSM-IV, because diagnostic instruments based on the DSM-5 [1] were not yet available at the development phase of this study. To enhance the clinical representativeness of the sample, exclusion criteria are kept to a minimum. Patients are only excluded if they currently: (1) meet DSM-IV-TR criteria for severe major depressive disorder or substance use disorder (other than smoking) that requires immediate treatment, psychotic disorder, or bipolar disorder; (2) have mental impairment or an organic brain disorder; or (3) had a change in medication type or dose in the six weeks before assessment or during treatment (see Fig. 2). The presence of other co-morbid diagnosis or previous treatment for OCD are not exclusion criteria. Potential participants will receive extensive information about the design and procedures of the study at the end of the clinical screening. Following informed consent, patients will be randomly assigned to the MCT or ERP condition. Randomization will be done by using www.randomization.com, an online generator which randomizes each individual to a treatment condition by using the method of randomly permuted blocks [24]. With randomly permuted blocks, participants are assigned to a treatment condition in blocks to ensure that equal numbers of individuals have been assigned to each treatment, not only at the end of the study but also at various intermediate time points. The generator also randomizes the block sizes (range = 1–4 per group), to ensure that it is unknown when a block is finished; it is not possible to guess the remaining treatment allocation. The process of allocation of cases to intervention conditions will be done by an independent employee of the participating mental health care center using the generated randomization plan. Patients will be allocated to treatment conditions in order of entry. The investigators and therapists have no insight in the randomization plan.

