#### Primary outcome

The primary outcome of interest for this MCT superiority study is OCD severity at post-treatment, which will be measured with the Y-BOCS [19], a semi-structured interview and the “gold standard” for measuring OCD symptoms. The Y-BOCS is a clinician-ratedsemi-structured interview designed to rate the severity of both obsessions and compulsion. The Y-BOCS consists of 10 items rated 0–4 (range = 0–40). The Y-BOCS has been shown to have good psychometric properties and is sensitive for measuring treatment effects [40]. Further, good internal consistency for both the subscales (obsessions and compulsions) and for the total score of the Y-BOCS has been reported [18].

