### Interventions

The interventions will be offered at the Anxiety Disorders Department of PsyQ, at which ERP is already delivered as treatment as usual for OCD. Both manual-driven treatments consist of up to 15 weekly sessions of 45 min duration. Treatment can be terminated earlier, when both patient and therapist agree that treatment goals are completed. A minimum of eight sessions will be managed as criteria for each patient to can be classified as treatment completer in the statistical analysis. Interventions will be delivered by nine staff psychologists, who are trained in CBT and who are familiar with the provision of ERP for OCD. Four of the participating therapists were trained by [name] and [name], experts in the field of MCT, preceding the start of a pilot study into the efficacy of MCT for OCD in which they participated as therapists [39]. The other five therapists will be trained in the provision of MCT for OCD by the fourth author (CH) preceding the start of this study. During the study, therapists will be supervised monthly by the fourth author (CH) in separate group sessions for ERP and MCT. In these 1-h supervision meetings, all current cases and therapy notes will be reviewed to ensure treatment quality and adherence. Treatment integrity will also be evaluated by means of randomly assessing recordings of treatment sessions against a session-by-session intervention checklist.

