Fixed effects in our model will be time, treatment, and their interaction. In case of missingness, we will add these variable(s) also as fixed effects. The Benjamini–Hochberg procedure is applied to the significances of the time*treatment interaction *p*-values (two-sided *p* < 0.05) of the different outcome measures. The time variable will be treated categorically, with the first post-baseline measurement as the reference category. To accommodate the modeling of correlation among repeated measurements, we impose a first order autoregressive (AR (1)) structure on the residuals. Next, the interaction effect between time and group will be explored by analyzing the estimated marginal means at different time points. We expect a significant interaction effect between time and group, which means that scores change differently over time in the two treatment conditions. More specifically, we expect a more negative time trend for MCT than for ERP, indicating that the measurement scores in the MCT condition decline more over time than in the ERP condition. To gain further insight into the statistical significance of the improvements achieved in the two treatment conditions, we will perform a least significant difference test with the estimated marginal means to compare changes between treatment conditions. In accordance with the linear mixed models, we expect a statistically significant decline in both treatment conditions between pretest and post-test, but no statistical differences between post-test and both follow-up measures. To allow for comparison with other studies into the effectiveness of ERP and MCT for OCD, Cohen’s *d* statistic ((mean 1 – mean 2) / pooled SD) will be employed to calculate within-group effect sizes (ES) for changes on outcome measures and to evaluate between-group differences. We will calculate Cohen’s *d* statistics for both intent-to-treat samples by using multilevel analysis with all available data and completer samples (our primary analysis: minimum of eight treatment sessions and no change in medication during treatment will be managed as criteria for each patient to can be classified as treatment completer). Based on previous research, we expect a large within-treatment ES for both treatment conditions (Cohen’s *d* > 0.8). We expect a medium between-group ES in favor of MCT. In addition, the clinical significance of treatment effects and amount of drop-out will be examined also to gain further insight into the clinical value of the two treatment conditions.

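### The analysis labelled primary is a completer analysis, selected on events after randomisation, so it does not preserve the randomised comparison

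*Protocol article*

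**What the plan says.** The primary endpoint is clear: "The primary outcome of interest for this MCT superiority study is OCD severity at post-treatment".

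The analysis set is given in the Outcomes part of the Statistical analysis section. Cohen's d is to be calculated in two samples. One is described as "intent-to-treat samples by using multilevel analysis with all available data". The other is "completer samples (our primary analysis: minimum of eight treatment sessions and no change in medication during treatment". Only the second carries the label of primary analysis, and the article nowhere gives that label to the intent-to-treat set.

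Three other sections bear on this:

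- Interventions repeats the session rule: "A minimum of eight sessions will be managed as criteria for each patient to can be classified as treatment completer in the statistical analysis". It also says "Treatment can be terminated earlier, when both patient and therapist agree that treatment goals are completed", with no minimum number of sessions for such an ending and no exemption from the eight-session rule.
- Participant enrollment and randomization lists among its exclusions patients who "had a change in medication type or dose in the six weeks before assessment or during treatment".
- Design provides for outcome data after drop-out: "In case of drop-out, measurements and interviews are also administered directly after treatment had ended whenever this is possible".

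**The concern.** Whether a patient reaches eight sessions, and whether medication changes during treatment, becomes known only after allocation. Either may depend on the therapy received. Selecting on them compares two groups that randomisation did not form.

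The protocol gives some reason to think that selection could differ by arm. Its background section reports "As approximately 30% of patients with OCD refuse ERP or drop out from treatment prematurely" and infers that ERP might be hard to tolerate. Its Discussion suggests that MCT may be less of a burden. If poor responders leave one arm more often, that arm looks better among completers.

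The session rule can also work the other way. A patient who stops before session 8 because patient and therapist agree that the goals are met counts as a non-completer. Any such loss would penalise the faster treatment. The two mechanisms pull in opposite directions, so the sign of the net bias is unknown.

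At stake is the main result of a superiority trial: a difference, or its absence, could reflect who stayed and not what the therapies did.

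**Working it through.** **1. The plan's own sample size.** Inputs from the Sample size section: d = 0.50, power 0.80, four measurement points, correlation 0.5, drop-out 20%. The two-sided 0.05 level comes from the Outcomes section. The repeated-measures formula for a time-averaged difference is

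n = 2(z₀.₉₇₅ + z₀.₈₀)² / d² × [1 + (m − 1)ρ] / m

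= 62.79 × (1 + 3 × 0.5)/4 = 62.79 × 0.625 = 39.24, so 40 per arm.

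With drop-out, 40 / 0.80 = 50 per arm, which matches the stated figure. The sample size is not in error on this point.

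**2. Bias of a completer contrast when there is no true difference.** Let p be the proportion of non-completers in an arm, and X the amount by which their outcome is worse than that of completers, in SD units and equal in both arms. The arm mean is then the completer mean plus pX. If the full arms have equal means, the completer means differ by

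bias = (difference in p) × X, in favour of the arm that loses more.

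The protocol gives neither quantity, so these values are assumptions:

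| Difference in p | X (SD) | Bias (SD) | Share of d = 0.5 |
|---|---|---|---|
| 0 | any | 0 | 0% |
| 0.10 | 0.5 | 0.05 | 10% |
| 0.10 | 1.0 | 0.10 | 20% |
| 0.20 | 0.5 | 0.10 | 20% |
| 0.20 | 1.0 | 0.20 | 40% |

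**3. Type I error.** Take 40 per arm and a baseline-adjusted comparison with correlation 0.5, so that the residual variance is 1 − 0.5² = 0.75. Then SE = √(2 × 0.75 / 40) = 0.194.

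- Bias 0.05: shift 0.05/0.194 = 0.26 SE, two-sided rejection about 6%.
- Bias 0.10: shift 0.52 SE, about 8%.
- Bias 0.20: shift 1.03 SE, about 18%.

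**4. Simulation of other patterns.** The assumptions were no true effect, 50 randomised per arm, 20% excluded per arm, exclusion driven by a latent variable correlated g with outcome, a t-test on those who remain, and 6,000 runs.

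| Pattern | Bias (SD) | Type I error |
|---|---|---|
| Same mechanism in both arms (g = 0.3) | about 0 | about 0.05 |
| One arm loses its worse patients, the other loses at random (g = 0.3 to 0.5) | 0.10 to 0.17 | 0.07 to 0.12 |
| One arm loses failures, the other early successes (g = 0.3 to 0.5) | 0.21 to 0.35 | 0.15 to 0.38 |

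Bias can therefore arise with equal exclusion rates if the reasons for exclusion differ. The last row is an extreme pattern, not a forecast.

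**5. Size of the completer set.** By the formula in step 1, power is 0.81 at 40 per arm, 0.75 at 35 and 0.69 at 30. The 20% allowance is for drop-out. If patients with a medication change, or an agreed ending before session 8, come on top of it, the completer set falls below 40 and power below 0.80.

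**The case against.** The strongest reply concerns how far the label reaches. It stands in a sentence on effect sizes, introduced as an aid to comparison with other studies. The hypothesis test is the time-by-treatment interaction in the mixed model, for which no set is named. The plan justifies that model by expected drop-out and its handling of missing data, adds pattern mixture models, and arranges to assess drop-outs. All of this suits an analysis of all available data. The reply stands in part: that the interaction test will be run on completers is an inference. But the only set called primary is the completer set, so the text needs correcting on either reading.

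Four stronger readings are tempting, and the protocol does not support them:

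- **Randomised patients are discarded altogether.** They are left out of the analysis labelled primary, but intent-to-treat results are planned too.
- **The exclusion for medication change during treatment removes patients even from the intent-to-treat set.** Outcomes uses the same event to separate completers from the intent-to-treat sample, which would be redundant if such patients had already gone. The two passages sit badly together, but that consequence is not shown.
- **Between 20% and 30% of patients will be lost from the primary analysis.** The 20% is a general drop-out allowance, and the 30% combines refusal with drop-out and concerns ERP only. Neither is a rate of failing the completer rule.
- **Non-completion will differ by arm and the fastest responders will be removed.** The remarks on burden are hedged, and the sample size uses one drop-out rate. Table 1 spreads both manuals over 15 sessions, and how often goals are met before session 8 is not stated. Both are possibilities.

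**Conclusion.** The concern holds in this form. The only analysis called primary selects patients on two events after randomisation, and followed as written it would take the main result of a superiority trial from a comparison that randomisation does not protect. This follows from the text and needs no assumption about the size of the bias.

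The size does rest on assumptions. A 10 to 20 point difference in non-completion and a 0.5 to 1.0 SD outcome gap give 0.05 to 0.20 SD, or 10% to 40% of the planned effect, and a type I error of about 6% to 18%. The low end is minor, and identical selection in both arms gives almost none. The direction is also open: if ERP lost more of its poor responders, the completer contrast would favour ERP, and if MCT had more early successes removed, it would be penalised as well. Opposite patterns would favour MCT.

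The change is worth requiring because the data and the model for the sounder analysis are already planned, and recruitment was still open, with 68 patients randomised.

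**What to change.** - In Outcomes, name as primary the baseline-adjusted mixed model of post-treatment Y-BOCS in all randomised patients as allocated, whatever the number of sessions attended or any medication change. Use the drop-out assessments that Design already provides for, and say that the hypothesis test uses this set.
- Make the completer analysis supportive. In its definition, count an ending agreed because goals were met as completion.
- Reconcile the exclusion criterion on medication change during treatment with the use of the same event as a completer criterion, so that it is clear that no randomised patient leaves the intent-to-treat set. This concerns the analysis population, not how medication is managed.

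The cost is a change of wording. The estimated effect may be somewhat diluted compared with completers. No new data are needed, and the planned 50 per arm stays.

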
#### Endpoints

The clinical significance of treatment effects will be examined using the procedures outlined by Jacobson and Truax [21]. Patients will be classified as recovered, if they score within the normal range on the Y-BOCS after treatment (cut-off point = 14) and display statistically reliable improvement on that measure (reliable change index = 10) [21]. Patients will be classified as improved but not recovered if they meet only one criterion. Patients will be classified as asymptomatic (a more stringent criterion for defining recovery) when they achieve a posttreatment score of ≤ 7 (indicating an almost total absence of OCD symptomatology), in addition to meeting the reliable change index. Further, diagnosis-free status will also be used as an index of clinically significant change.

## Discussion

MCT is a relatively new treatment for OCD, based on a metacognitive model that states that, rather than the intrusive thoughts and compulsive behaviors, it is in fact beliefs about the meaning and significance of obsessive thoughts on the one hand and beliefs about the need to conduct rituals and neutralizing behaviors on the other hand that are crucial for the development of OCD As a result, interventions should be targeted at these metacognitive beliefs. Our hypothesis is that MCT is more efficacious in the treatment of OCD than the current “gold standard” psychological treatment for OCD, ERP. Since there is a wide variation in symptomatology between OCD patients, and beliefs about intrusions and compulsions are comparable for each subtype, it may be that MCT is particularly well suited in the treatment of this disorder. Moreover, it may be that MCT is less burdensome since it does not include prolonged exposure to anxiety provoking stimuli. So far, five relatively small studies suggest that MCT might be an efficacious treatment for OCD and may be even more efficacious than the current “gold standard,” ERP [12, 16, 33, 35, 39]. We presented the rationale and design of a RCT assessing the relative efficacy of ERP and MCT for OCD. To our knowledge, this is the first long-term RCT to explore whether MCT produces better results than ERP.

The study has several strengths, including randomization of patients to two active treatment conditions, use of an unselected, clinically representative sample of OCD patients, and long-termfollow-up assessments.

However, the current study also has limitations. Treatment conditions might be contaminated as participating therapists will deliver both ERP and MCT. It might also be difficult to maintain treatment integrity as both treatments will be conducted by therapists who work within a routine outpatient community mental health center. We aim to minimize these limitations by means of reviewing all active cases in consultation meetings and careful checking of treatment integrity.

### Trial status

This study received ethical approval from the Medical Ethical Committee of the Leiden University Medical Centre (LUMC) on 21 October 2014. The first patient enrolled on 6 February 2015. Sixty-eight participants are randomized so far. We are still recruiting patients and have planned to close the inclusion at the end of 2019.

## Abbreviations

AR (1): First order autoregressive
BARI: Beliefs About Rituals Inventory
BDI: Beck Depression Inventory
CBT: Cognitive behavioral therapy
CT: Cognitive therapy
DM: Detached mindfulness
DSM: Diagnostic and Statistical Manual of Mental Disorders
ERP: Exposure and response prevention
ES: Effect size
LUMC: Leiden University Medical Centre
MAR: Missing at Random
MCT: Metacognitive therapy
MNAR: Missing Not at Random
OBQ: Obsessive Belief Questionnaire
OCD: Obsessive compulsive disorder
Padua-IR: Padua Inventory-Revised
RCT: Randomized controlled trial
SCID-I: Structured Clinical Interview for DSM Axis I Disorders
SCL-90: Symptom Checklist
SD: Standard deviation
SPIRIT: Standard Protocol Items: Recommendations of Interventional Study’s
SPSS: Statistical Package for the Social Sciences
SSRI: Selective serotonin reuptake inhibitors
TAF: Thought action fusion
TCRF: Treatment Change Recording Form
TEF: Thought event fusion
TFI: Thought fusion instrument
TOF: Thought object fusion
WHOQOL: World Health Organization Quality of Life
Y-BOCS: Yale-Brown Obsessive Compulsive Scale
